## Abstract

Obstructive sleep apnea (OSA) is associated with a number of adverse health effects, particularly on brain health. Chronic sleep disruption caused by OSA can adversely affect cognitive health. Exercise is recommended as a non-pharmacological intervention for patients who are intolerant to continuous positive airway pressure (CPAP) and has been shown to have beneficial effects on brain health and cognitive function. This protocol aims to investigate the effects of a 12-week tele-exercise program on cognitive function and specific parameters of brain activity, including brain metabolism and oxygenation, in patients with OSA. The project aims to demonstrate the multidimensional relationship between exercise, cognition, and brain oxygenation/metabolism. Our local ethics committee has approved the study. Our population sample (Group A, OSA with cognitive impairment (CI) and tele-exercise; Group B, OSA with CI and no tele-exercise; Group C, OSA without CI and no tele-exercise) will undergo assessment both before and after a 12-week tele-exercise intervention program. This assessment will include a comprehensive battery of subjective and objective assessment tests. Data will be analyzed according to group stratification. We hypothesize a beneficial effect of tele-exercise on sleep and cognitive parameters, and we are confident that this study will raise awareness among healthcare professionals of the brain health benefits of exercise in patients with low compliance to CPAP treatment. The protocol of our manuscript entitled "The impact of a 12-week tele-exercise program on cognitive function and cerebral oxygenation in patients with OSA: Randomized Controlled Trial -Protocol Study" has been registered on ClinicalTrials.gov with ID NCT06467682.

## Background

Obstructive sleep apnea (OSA) is characterized by repeated episodes of obstruction of the upper airway during sleep causing intermittent hypoxia, sleep fragmentation, hypercapnia, and sympathetic hyperactivity (1). These factors contribute to various adverse health effects, notably impacting brain health. Hyperarousability in OSA can negatively impact sleep in the macro- and micro-architecture and sleep continuity, both of which are important players in neurogenesis, brain plasticity, alertness, and the processes of memory formation and consolidation (2). Thus, chronic sleep alterations caused by OSA can negatively impact cognitive health (2). Both sleep fragmentation and intermittent hypoxia affect brain structure and function, increasing susceptibility to neurodegenerative diseases (3). The prevalence of OSA is increasing as it is conjoined with obesity and tends to elude clinicians’ attention, with definitive diagnosis achieved in only 10% of the population. Approximately 80% of OSA patients report reduced performance at work (4), while 40% of the risk of dementia can be attributed to modifiable risk factors such as physical inactivity (5).

Exercise provides a wide range of benefits to the general population by improving cardiorespiratory and metabolic profiles (6). Exercise is recommended as a low-cost, easy-to-administer, non-pharmacological intervention with beneficial effects on brain health and cognitive function, mainly by improving sleep architecture, enhancing the neurovascular oxygenation process and cerebral oxygenation, reducing sympathetic overactivity, and improving vascular function at rest and during exercise or mental stress (6, 7). In addition, studies have shown that exercise can mitigate various aspects of brain deterioration, such as reduced blood flow and lack of important factors [e.g., brain-derived neurotrophic factor (BDNF)]. These factors play a key role in nourishing the brain's neurons and promoting the growth and development of new neurons and synapses. Based on classical theories (8), physical exercise can be considered an enhancing environmental factor that promotes neuroplasticity (increasing blood and oxygen flow to the brain, stimulating neuron growth, and increasing nerve conduction). In addition, exercise has beneficial biological and psychological effects on the brain, cognitive function (9), and sleep (10) and triggers potent neuroplastic phenomena, partly mediated by epigenetic mechanisms (9). Therefore, long-term exercise produces significant and lasting benefits such as improved cerebral neurovascular dynamics, cerebrovascular function, cognition, and neuroplasticity in various brain regions, parameters related to cerebral oxygenation and metabolism, which can be assessed by functional near-infrared spectroscopy (fNIRS) (11, 12). In addition, exercise intensity correlates with cognitive functions such as memory improvement after 12-week programs of both aerobic and resistance exercise (13, 14). The effectiveness of different exercise programs has not been well established, and some studies suggest that supervised vs. self-selected programs may have similar outcomes (15, 16). In addition, the types of exercise programs in patients with OSA have been addressed in the literature (6). However, there is a significant dropout rate from face-to-face exercise programs, especially if they last several weeks, due to high cost, difficulty, and/or lack of access to rehabilitation centers (6). Tele-exercising could be a key to overcoming this important limitation. However, data on tele-exercise is scarce.

This protocol aims to investigate the effects of a 12-week tele-exercise program on cognitive function and specific parameters of brain activity, including brain metabolism and oxygenation, in patients with OSA. The project aims to highlight the multidimensional relationship between physical exercise, cognition, and brain oxygenation/metabolism.

## Methods

This study is a randomized controlled trial and has been approved by the National Bioethics Committee of Cyprus (EEBK/EP 2023/60), the State Health Services Organization of Cyprus (05.34.001.002/44/23), and ClinicalTrials.gov (NCT06467682). Written informed consent will be obtained from patients in accordance with the tenets of the Declaration of Helsinki (17) and the regulations of the European Parliament and Council of the European Union (18).

### Study population

This study will include newly diagnosed patients with OSA, and participants will be recruited from the Sleep Apnea Outpatient Clinics and Sleep–Wake Outpatient Clinics of the Nicosia General Hospital. We will perform a screening cognitive test via the Montreal cognitive assessment (MoCA) questionnaire to identify individuals with cognitive impairment (CI). Patients with OSA and CI will be randomized into two groups: The OSA group with CI who will undergo the tele-exercise program (TE) (Group A) and the OSA group with CI who will not undergo the TE (Group B). A third matched group (Group C) of OSA patients without cognitive impairment will act as a second control group. Group A will perform a tele-exercise program on the Unique Safe Tele-Exercise Project platform (https://ustep.gr), for 12 weeks. All patients who will be enrolled in our study will not receive continuous positive airway pressure (non-CPAP) treatment (delayed therapy) (Graphical Abstract).

The inclusion criteria for this study will be the following: age ≥18 to ≤70 years, apnea–hypopnea index (AHI) ≥15 events/h, no contraindications (e.g., unstable angina during the previous month, myocardial infarction in the previous month, resting heart rate >120 bpm, systolic blood pressure >180 mmHg, and diastolic blood pressure >100 mmHg) for the 6 min walk test (6MWT) (19, 20), body mass index (BMI) <40 kg/m^2^, no daily physical workload, no active self-reported symptoms (fatigue and dyspnea) (21, 22, 23), and pregnancy. Patients with pre-existing musculoskeletal disability were excluded because their condition may affect maximal exercise capacity (24). All participants should be able to read and understand Greek.

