### Statistical analysis

For the sample size calculation of this study, a power of 85% and a confidence interval of 95% were adopted (G*Power software 3.1), with an estimated type 1 error value of 5%, given the lack of previous studies investigating the effects of a tele-exercise program in patients with OSA. We determined a sample size of 20 patients for each group. The Kolmogorov–Smirnov test will be used to assess data normality for continuous variables. ANOVA analysis of variance will be applied to compare the groups before and after the intervention period. Relationships between continuous variables will be assessed via Spearman's rho and Pearson's R correlation coefficients for non-parametric and parametric variables, respectively. Differences between cutoff strata will be assessed via the independent samples *t*-test or Mann–Whitney *U*-test where appropriate. Analysis of fNIRS data will be based on a boxcar general linear model and a custom MATLAB (MathWorks, Natick, MA, USA) script (44). A *p*-value of <0.05 will be considered statistically significant for all tests. The IBM SPSS 21 statistical package (SPSS Inc., Chicago, IL, USA) will be used for all statistical analyses.

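### The stated group ANOVA does not use the matching of Group C, so single-timepoint contrasts with C are conservative if the matching factors predict the outcome

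*Protocol article*

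**What the plan says.** - Study population: "Patients with OSA and CI will be randomized into two groups" (Groups A and B). Group C is not randomised: "A third matched group (Group C) of OSA patients without cognitive impairment will act as a second control group". The article does not say which variables are matched, in what ratio, individually or by frequency, or whether the match is to A, to B or to both.
- Assessment: every outcome is measured at baseline and at 12 weeks. For the fNIRS outcomes the article plans a comparison across all three groups, so contrasts involving C are intended.
- Statistical analysis, group comparison: "ANOVA analysis of variance will be applied to compare the groups before and after the intervention period". Whether this is a one-way or a repeated-measures ANOVA, and whether it has covariates, is not stated.
- Statistical analysis, fNIRS: "Analysis of fNIRS data will be based on a boxcar general linear model", again with no mention of the matching.
- Statistical analysis, size: "We determined a sample size of 20 patients for each group".

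**The concern.** Matching is a design feature, and its benefit in precision is obtained only if the analysis uses it. When C is chosen to resemble the comparison group on factors that predict the outcome, those factors contribute little or nothing to the difference in means. An ANOVA without them still counts their variance as residual noise, so the standard error it reports is larger than the true one. Intervals against C are then wider than they need be, and a real difference between impaired and unimpaired patients is more easily missed. With 20 patients per group there is little precision to spare.

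**Working it through.** **Inputs from the article.** 20 patients per group, power 85%, alpha 5% (Statistical analysis). Two-sided testing is assumed, because sidedness is not stated.

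**The plan's own figure.** No effect size or SD is given, so 20 per group can be neither reproduced nor refuted. For a two-sided two-sample t-test, 20 per group at 85% power corresponds to a standardised difference of 0.97.

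**Assumed input.** The share *s* of outcome variance explained by the matching factors is not given. It is taken as 10, 20, 30 and 40%.

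**Single-timepoint contrast (baseline or 12 weeks).** Write each outcome, with total variance 1, as √*s* × matching score + √(1 − *s*) × independent error, with the score equal in matched patients.

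- True variance of the difference in means: 2(1 − *s*)/20.
- Variance the unadjusted analysis estimates: 2/20.
- Ratio of standard errors, unadjusted to adjusted: 1/√(1 − *s*).
- Ratio of interval half-widths, including the t quantiles (38 df, 2.024; 37 df after one covariate, 2.026): (2.024/2.026)/√(1 − *s*).
- Approximate type I error of the unadjusted test: 2·P(T with 38 df > 2.024/√(1 − *s*)).

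For *s* = 20%: 1/√0.8 = 1.118; the half-width ratio is 1.118 × 0.999 = 1.117; the critical value becomes 2.024 × 1.118 = 2.263, which gives 2.9%.

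The type I error and power below come from a simulation of 40,000 trials per setting (20 matched pairs, unadjusted t-test versus ANCOVA on the score). Power is for an assumed difference of 0.8 SD.

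| *s* | Interval too wide by | Type I error, formula | Type I error, simulated | Power unadjusted | Power adjusted |
|---|---|---|---|---|---|
| 10% | 5% | 3.9% | 4.0% | 70% | 74% |
| 20% | 12% | 2.9% | 3.0% | 71% | 79% |
| 30% | 19% | 2.0% | 2.0% | 73% | 84% |
| 40% | 29% | 1.3% | 1.4% | 74% | 89% |

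At *s* = 0 the two powers are both about 70%, so adjusting costs almost nothing when the factors turn out to be unrelated to the outcome.

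**Type of matching.** With frequency matching (four strata of five, no pairs) and *s* = 20/30/40%, the interval is 12/20/30% too wide, the type I error is 3.1/2.2/1.5%, and power is 71/72/72% unadjusted versus 79/84/89% adjusted. The result does not depend on one-to-one pairs.

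**Contrast of change from baseline.** If the score has the same effect at both times, √*s* × score cancels in the 12-week minus baseline difference. The change then contains none of the matching variance, and there is nothing for adjustment to recover. With an assumed pre-post correlation of 0.6, the simulated type I error of the unadjusted test on change is 5.0/5.1/4.9/5.1% for *s* = 10/20/30/40%, which is nominal.

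**A versus B.** These arms are formed by randomisation and not by matching, so none of the above applies.

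**The case against.** Several points on the other side stand.

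- A reader might infer that every planned comparison treats the groups as independent samples. The text does not support that. The independent-samples t-test and Mann–Whitney test are assigned to cutoff strata, not to Groups A, B and C, and the form of the ANOVA is open. What can be said is that none of the listed methods mentions the matching, and that a standard one-way or repeated-measures ANOVA has no matching term unless one is added.
- Every outcome is measured before and after. If the contrast with C is one of change, stable matching factors largely cancel and the loss disappears. This limits the point to comparisons at a single time.
- The size cannot be determined from the article, because the matching variables and their relation to the outcomes are not given.
- If matching is one to one and a paired t-test (19 df) were used, it would be less precise than the independent test when the within-pair correlation is below about 0.06. Covariate adjustment, with 37 df, does not carry that penalty.
- A reader might also infer that a non-significant A versus C difference would be presented as cognition returning to normal. The article plans no equivalence or normalisation claim and calls C only a second control group. Such a misreading would be a separate error that covariates do not cure.
- The article is condensed, and a fuller protocol or analysis plan that is not shown may already specify the adjustment. That lowers the weight of the point. It does not remove the mismatch between a matched group and the group test that the article names.

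**Conclusion.** The point holds in a limited form and is minor. Group C is selected by matching, and the stated group ANOVA makes no use of it. If the matching factors explain 10 to 40% of outcome variance (an assumption), unadjusted intervals for single-timepoint contrasts with C are about 5 to 29% too wide. The type I error then falls to between about 4% and 1%, and power for a 0.8 SD difference is about 4 to 15 percentage points lower than with adjustment. The error is in the conservative direction: under this model false positives are not inflated. For change from baseline the loss is small or absent when the factors act equally at both times. The randomised A versus B comparison, which carries the effect of tele-exercise, is untouched.

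**What to change.** Add to Statistical analysis that, in comparisons with Group C, the variables used for matching enter the model as covariates, or that a matched-set term is included if matching is one to one. Name those variables and the type of matching, since the model cannot be written without them. Report the adjusted difference with its 95% confidence interval, and present it separately from the randomised A versus B result so that the two are not read as equal evidence. The cost is a sentence or two of plan wording and a few degrees of freedom. No new data are needed, because the matching variables are known when Group C is selected.

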### Assessment

All participants will be asked to sign a consent form prior to any study-related assessment. The baseline assessment will be conducted before the randomization of participants into groups, and the same assessment protocol will be used immediately after the 12-week intervention period (IP).

The study-related assessments include the following. (a) *Polysomnography study* (PSG): all patients will undergo a home-based sleep study using a portable PSG device (SOMNOtouch RESP, SOMNOmedics, Germany) for the investigation of sleep quality and the classification of sleep apnea severity (25). (b) *Questionnaires*: (i) Montreal cognitive assessment (MoCA) to investigate the cognitive status and classify participants into groups (26), (ii) two-part trail making test (TMT A and *Β*) to assess shifting attention and selective attention (27), (iii) Pittsburgh sleep quality index (PSQI) to assess the quality and patterns of sleep (28), (iv) Epworth sleepiness scale (ESS) to assess daily sleepiness levels (29), (v) Karolinska sleepiness scale (KSS) to assess the situational sleepiness (30), and (vi) work ability index (WAI) to investigate the ability to return to work without restrictions (31). (c) *Pulmonary function test*: standard spirometry testing (32) followed by the diffusing capacity of the lungs for carbon monoxide (MasterScreen-CPX, VIASYS Healthcare, Germany) according to ATS/ERS guidelines (33) and respiratory muscle strength (Airofit PRO, Copenhagen, Denmark) (34). (d) (i) *Anthropometric characteristics*: anthropometric characteristics such as body height, chest circumference in maximal inhalation and exhalation, neck circumference, and waist–hip ratio will be recorded (Seca 700 and 201, Hamburg, Germany) (35); (ii) *body composition*: body mass, muscle mass, percentage of body fat, visceral fat score, total body water, etc. will be recorded via bioelectrical impedance analysis (Tanita MC-980, Arlington Heights, IL, USA) (35). (e) *Physical fitness test*: we will use physical fitness tests to assess exercise capacity via 6MWT (19) and 30 s sit-to-stand test (36). Before, at the end of tests, and at the first minute of recovery, blood pressure, arterial O_2_ saturation, and heart rate will be recorded, and patients will self-assess for dyspnea and lower limb fatigue via CR-10 Borg scale (37). The isometric power will be recorded via a handgrip strength test (KFORCE, Kinvent Estonia) (23). (f) *Cardiopulmonary exercise testing (CPET) parameters*: we will record the cardiopulmonary (i.e., oxygen consumption, carbon dioxide production, ventilation, tidal volume, and breath frequency end-tidal partial pressure of carbon dioxide and oxygen) and metabolic parameters, via portable device COSMED K5 (38) before, during, and at the first minute of recovery of each physical fitness test (6MWT and 30 s sit-to-stand test). (g) *Cognitive test*: we will use the FitLight Trainer (Sports Corp., Ontario, Canada) integrated into wireless unit touch and motion sensors. All participants will perform tests of a pre-planned motion structure to assess perceptual skills, executive functions, and brain sensory functions such as reactivity, movement accuracy, and visuospatial capacities (39, 40). (h) *Functional near-infrared spectroscopy (fNIRS) parameters*: we will use the fNIRS device (BIOPAC Systems, Inc. Goleta, CA, USA) to assess and record cerebral oxygenation-oxygenated and deoxygenated hemoglobin (fNIRS) before, during, and after physical fitness and cognitive tests (41, 42).

Study-related outcomes include the following. (a) *PSG study outcome*: for this aim, we will compare several sleep/wake questionnaires, and various polysomnographic quantitative and qualitative parameters at baseline and 12-week follow-up will be assessed, e.g., change in sleep architecture, sleep staging features, and respiratory features in PSG between baseline and 12-week follow-up. (b) *Questionnaire*s *on the cognitive outcome*: (i) verbal episodic memory based on subdomains of the encoding process and immediate recall, free and cued recall, and recognition and delayed recall; (ii) score in a serial verbal learning task, with control of encoding and recall, according to the modified procedure of Grober and Buschke (43); and (iii) working memory with subdomains the auditory information processing speed, flexibility, and working memory span. (c) *CPET parameters outcome*: to investigate the extent to which tele-exercise improves cardiopulmonary metabolic parameters in patients with OSA at baseline and 12-week follow-up in participants with non-CPAP treatment. (d) *fNIRS outcomes*: cerebral oxygenation according to fNIRS-based measure levels of oxyhemoglobin (HbO) and deoxygenated hemoglobin (deoxy-Hb). For this aim, we will compare cerebral oxygenation values fNIRS at baseline and following a 12-week follow-up in the abovementioned three groups of patients.

All the above assessments will be performed at baseline and 12-week follow-up.

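### If MoCA change is compared across all three groups, regression to the mean from sorting patients on baseline MoCA can pass for cognitive change; the randomised A-versus-B comparison is not affected

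*Protocol article*

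**What the plan says.** All places are in the Methods of the protocol article.

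- **Sorting.** Study population: "We will perform a screening cognitive test via the Montreal cognitive assessment (MoCA) questionnaire to identify individuals with cognitive impairment (CI"). The article prints no cut-off.
- **Same instrument in the battery.** The Assessment section lists the "Montreal cognitive assessment (MoCA) to investigate the cognitive status and classify participants into groups".
- **Repeat.** Baseline assessment comes before randomisation, and "the same assessment protocol will be used immediately after the 12-week intervention period (IP"). The end of the section confirms this: "All the above assessments will be performed at baseline and 12-week follow-up". No second pre-treatment MoCA is described.
- **Groups.** "Patients with OSA and CI will be randomized into two groups", which gives A (tele-exercise) and B (no tele-exercise). Group C is not randomised: "A third matched group (Group C) of OSA patients without cognitive impairment will act as a second control group". The matching variables are not given.
- **Cognitive outcomes.** The outcome list in the Assessment section starts with "verbal episodic memory based on subdomains of the encoding process and immediate recall, free and cued recall, and recognition and delayed recall" and goes on to a serial verbal learning task and working memory. MoCA is not named there.
- **Analysis.** Statistical analysis: "ANOVA analysis of variance will be applied to compare the groups before and after the intervention period". The sentence does not separate the randomised pair A and B from Group C.

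**The concern.** A and B are chosen because their MoCA was low on the day of classification, and C because it was normal. Part of each score is measurement error. Selection from below the cut-off favours patients with negative error that day, and selection from above it favours positive error. At retest the error is drawn afresh, so A and B rise on average and C falls, although nobody has changed.

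When the classifying score is also the baseline value, this shift is part of every change score, with opposite sign on the two sides of the cut-off. A three-group comparison of change, or A against C, could then be reported as Group A improving or closing the gap to unimpaired patients, when only selection error has washed out. The trial's declared aim is cognitive function and MoCA is measured at both visits, so a report of MoCA change is foreseeable.

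**Working it through.** **Inputs from the article.** 20 patients per group; significance at p<0.05 (taken as two-sided). The article prints no figure for MoCA change, so there is none to reproduce.

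**Assumed inputs, none of them in the article.** Cut-off below 26 (25.5 on a continuous scale); MoCA SD 3; clinic mean 24-25; test-retest correlation r of 0.9, 0.8 or 0.7; no true change; no practice effect; Group C from the same clinic population; matching not modelled.

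**Step 1: expected drift.** With mean μ, SD σ, cut-off c and a = (c − μ)/σ:

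- mean baseline below the cut-off = μ − σ·φ(a)/Φ(a)
- mean baseline above the cut-off = μ + σ·φ(a)/(1 − Φ(a))
- expected change with no true change = (1 − r)·(μ − mean baseline of the selected group)

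For μ = 25, σ = 3, r = 0.8: a = 0.5/3 = 0.167, φ(a) = 0.393, Φ(a) = 0.566.

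- Groups A and B: 3 × 0.393/0.566 = 2.08 below the mean, so the drift is 0.2 × 2.08 = +0.42 points.
- Group C: 3 × 0.393/0.434 = 2.72 above the mean, so the drift is −0.2 × 2.72 = −0.54 points.
- Spurious gap in change, A or B against C: 0.42 + 0.54 = 0.96 points.
- A against B: 0.42 − 0.42 = 0.

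**Step 2: rough size of the false-positive rate.** In this scenario the SD of change below the cut-off is 1.84. Using it for both groups, the standard error of the A-minus-C difference is 1.84 × √(2/20) = 0.58, and 0.96/0.58 = 1.65. The chance of exceeding 1.96 is about P(Z > 0.31) = 38%.

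**Step 3: simulation.** Scores were rounded and capped at 30, with 20 per group and 2,000 trials per row. The three-group test is a one-way ANOVA on change, which for two time points is the group-by-time test.

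| Mean | r | Drift A/B | Drift C | Three-group p<0.05 | A vs C p<0.05 | A vs B p<0.05 |
|---|---|---|---|---|---|---|
| 24 | 0.9 | +0.17 | −0.37 | 21% | 24% | 4.8% |
| 24 | 0.8 | +0.33 | −0.70 | 41% | 40% | 6.0% |
| 24 | 0.7 | +0.48 | −1.05 | 59% | 59% | 5.5% |
| 25 | 0.9 | +0.23 | −0.30 | 22% | 24% | 5.4% |
| 25 | 0.8 | +0.43 | −0.58 | 40% | 41% | 4.7% |
| 25 | 0.7 | +0.64 | −0.82 | 56% | 56% | 5.8% |

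The fifth row gives 41% for A versus C, against the hand figure of 38%.

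**Step 4: wider assumptions.** With mean 24-26, SD 2.5-3.5 and r 0.7-0.9, the formula gives a drift of +0.11 to +0.94 in A and B, −0.17 to −1.14 in C, and a gap of 0.40 to 1.72 points. The size moves a good deal; the direction is the same for every r below 1.

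**The case against.** **MoCA is not a listed outcome.** This stands. The outcome list names other cognitive measures, and MoCA is tied to follow-up only by the general sentence that all assessments are repeated. A reader might infer that the plan declares MoCA change as an outcome with the screening score as its baseline; the article says neither. The screening test under Study population could also be a separate administration. A single administration is still the plainer reading, because the MoCA listed in the battery is the one said to classify participants.

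**The exercise effect is protected.** This also stands. A and B are randomised from the same MoCA-selected pool and drift equally. A reader might infer that the estimate of the tele-exercise effect is biased; it is not.

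**No within-group test is specified.** Correct. A false-positive rate for a before-after test in Group A alone would describe an analysis that the article does not name, so the case does not rest on one. The three-group comparison is the nearest match to the stated ANOVA.

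**The size is assumed.** Correct: cut-off, mean, SD and reliability are all absent from the article. A practice effect would add to the rise in A and B and could mask the fall in C. Matching could alter the figures by an unknown amount.

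**The choice of baseline value belongs in the analysis plan.** Partly. Which value to analyse can be settled there, but a second baseline MoCA cannot be created later if none was taken.

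**Conclusion.** The point holds in a limited form. On the plain reading, one baseline MoCA both forms the groups and starts the change score, and the stated ANOVA does not keep the MoCA-selected, non-randomised Group C apart from the randomised pair. If that ANOVA is run on MoCA across three groups, a group-by-time result can arise from selection alone, in roughly 20-60% of trials under the stated assumptions.

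The documents do not support a conclusion that the trial's cognitive results as a whole are compromised. A versus B is unbiased. The memory tests, TMT, FitLight and fNIRS are not the selection variable and are affected only as far as their baseline error correlates with the MoCA error.

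**What to change.** Add to the Statistical analysis section one of the following:

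1. Any conclusion from MoCA change rests only on the randomised A-versus-B comparison at 12 weeks, adjusted for baseline; comparisons with Group C and within-group MoCA change are descriptive.
2. MoCA serves as classifier only, and conclusions on cognition rest on tests not used for selection: the memory tests in the outcome list, TMT and FitLight.

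Optionally, if MoCA change is wanted for all three groups, take its baseline value from a separate administration after impairment has been classified but before A/B randomisation. That order keeps to the article's rule that baseline precedes randomisation. If two administrations are already planned, one sentence saying which is the analysis baseline is enough.

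Either wording change costs no data collection; the optional repeat costs one short questionnaire per patient. The downside is that MoCA change loses standing as evidence outside A versus B.
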